### Intervention

At the fetal heart monitoring studio, we will ask the participants to add our Wechat account, and the subsequent communications and relevant questionnaire distribution will be carried out through Wechat chat software. In the T_1_ stage, participants will complete a series of intervention questionnaires. Participants in the intervention group will be asked to write down three good things that have happened during the day every 2 days, with weekly specific themes. Participants in the control group will only have to write about three things that come to mind first that are related to the same theme. To improve the compliance and interest of the participants, we will set up different instructions and themes for them weekly (table 1). Meanwhile, if a participant forgets to write, we will send out hints if they fail to complete the questionnaires. When the participant is unwilling to take the initiative to fill in the questionnaire, we will ask for reasons and send encouraging messages (eg, about the benefits of participating in the project). For ethical considerations of avoiding excessive disturbance, the participants will be regarded as loss-to-follow-up, after three non-responses.

**Table 1 T1:** Instructions for the intervention and control groups

Week	Topic	Instructions for the intervention group	Instructions for the control group
1	My baby	Please recall three good things that happened to you today related to you and your baby, and record them with the reasons why they happened. Here are some examples: My baby is moving today, and my baby is growing healthily. I saw a cute baby picture today, and my baby may be cuter. I bought baby’s little clothes today, they are so small and cute.	Please record the first three baby-related events that come to your mind today, and record them and the reasons why they happened. Here are some examples: I suddenly thought that it is not easy to have a child. I had the maternity check-up today.
2	Nature and me	Please recall three good things that happened to you today related to nature, and record them with the reasons why they happened. Here are some examples: I heard a bird chirping on the road today, is it saying hello to me? The small flower we planted is blooming, we have taken good care of it. The sky is blue today, and there are traces of airplanes flying over.	Please record the first three nature-related events that come to your mind today, and record them and the reasons why they happened. Here are some examples: It’s raining today, and the air is wet. I watered the flowers at home.
3	My family	Please recall three good things that happened to you today related to your family, and record them with the reasons why they happened. Here are some examples: My husband is very considerate, and I feel very happy. My mother and mother-in-law specially cook duck for me, they always love me very much. All the people I love and I am expecting the baby together. My friends also told me just take it easy and not to be nervous.	Please record the first three family-related events that come to your mind today, and record them and the reasons why they happened. Here are some examples: My husband and I had dinner with our parents today. A good friend of mine got married today.
4	My future	Please recall three good things that happened to you today related to the future, and record them with the reasons why they happened. Here are some examples: Today, I saw other people’s little kids, this time next year I can have my own baby! The weather forecast says the weather will be good, I'm looking forward to sunshine tomorrow. Tomorrow my favourite TV series will be updated.	Please record the first three future-related events that come to your mind today, and record them and the reasons why they happened. Here are some examples: We're going for a check-up tomorrow. Tomorrow my mother-in-law is coming to visit us.
5	My life	Please recall three good things that happened to you today related to your life, and record them with the reasons why they happened. Here are some examples: Today, I listened to my favourite songs, which gave me a lot of inspiration and memories. Today, I found a gentle sentence on my phone, which said, ‘I was born mediocre, and I was born proud. Let’s be a happy ordinary person’. The emoticons my friend sent me today were so cute, I thought they were very interesting and funny.	Please record the first three life-related events that come to your mind today, and record them and the reasons why they happened. Here are some examples: I watch videos on the phone for an hour today. I watched a TV series with my husband this evening.

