### Recruitment

The study will be conducted in the Women’s Hospital School of Medicine at Zhejiang University. We will include primiparous pregnant women at 34–38 gestational weeks. The exclusion criteria are as follows:

Women with no intention to give birth in a designated hospital.Women not giving birth for the first time.Women with a disease that prevents breastfeeding (cardiac insufficiency, infectious diseases, neurological or cognitive damage, etc)Pregnant women with more than one fetus.

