### Sample size

Based on the results of the pilot study, statistical power (1−β) of 80%, and a two-tailed significance level (α) of 0.05, we calculated the targeted sample size with a two-sample t-test allowing unequal variance. Given the breastfeeding behaviour score (LATCH) was 12.72 in the intervention group (SD=2.33) and 12.06 in the control group (SD=1.51), the theoretical sample size was shown as N1=N2 = 141. Considering a dropout rate of 20%, the ultimate sample size needed was estimated at 353 individuals.

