### Evaluation and outcomes

Primary outcomes will include exclusive breastfeeding and on-demand feeding during postnatal hospitalisation. Exclusive breastfeeding means that the baby is not given any liquid or solid food other than breast milk. This indicator will be included in the postnatal questionnaire and also be double-checked in the hospital care records of formula. On-demand feeding means breastfeeding according to the baby’s needs. Since the infant’s early urination reflects breastfeeding, changing diapers 6–8 times a day in the early postpartum period is considered feeding on demand.

Secondary outcome indicators will mainly include other breastfeeding behaviours during postpartum hospitalisation (first postnatal food for babies is breast milk; LATCH breastfeeding score), lactation-related hormone secretion (prolactin and IGF-I) and postpartum breastfeeding intention and postpartum emotion.

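### Three non-responses during the writing task count as loss to follow-up, which would ordinarily end outcome collection for non-adherers although some outcomes, including exclusive breastfeeding, can still be obtained

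*Protocol article*

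**What the plan says.** The Intervention section of the protocol article asks the intervention group to "write down three good things that have happened during the day every 2 days, with weekly specific themes". For the other arm, "Participants in the control group will only have to write about three things that come to mind first", on the same weekly theme. On missed entries it says that "if a participant forgets to write, we will send out hints if they fail to complete the questionnaires". Unwilling women are asked why and sent encouragement. Then, with the stated aim of not disturbing women too much, "the participants will be regarded as loss-to-follow-up, after three non-responses".

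Other sections bear on what is lost when a woman is classed this way:

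- **Evaluation and outcomes.** The primary outcomes are exclusive breastfeeding and on-demand feeding during the postnatal stay. Exclusive breastfeeding is asked in the postnatal questionnaire and will "also be double-checked in the hospital care records of formula". On-demand feeding is judged from the daily number of diaper changes; no record source is given for it.
- **Recruitment.** Women who do not intend to deliver in a designated hospital are excluded.
- **Data collection and follow-up.** Ward nurses draw the blood for prolactin and IGF-I. The postpartum questionnaire is completed 1 week after delivery, and all questionnaires are sent through WeChat.
- **Sample size.** The target is raised from 141 per arm to 353 in total for 20% dropout.
- **Data analysis.** Two-group tests are named. Nothing is said about women declared lost.

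**The concern.** Not completing the writing task, or not answering messages about it, is a post-randomisation event that concerns adherence. Loss to follow-up is a different event: the outcome cannot be obtained. The protocol's rule converts the first into the second. Its stated reason supports ending the reminders; it gives no ground for ending outcome collection.

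Two features make this more than a matter of labels. First, recalling good things and noting whatever comes to mind are different tasks, so persistence can differ by arm. Second, persistence plausibly follows mood and motivation, and the trial's own hypotheses link emotions to breastfeeding. If women are removed at different rates by arm, and those removed have different feeding outcomes from those kept, the comparison is no longer the randomised one and can show or hide an effect. Data never collected cannot be restored by any later analysis plan.

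**Working it through.** **The plan's own figure.** Inputs from Sample size: LATCH 12.72 (SD 2.33) versus 12.06 (SD 1.51), difference 0.66, "statistical power (1−β) of 80%, and a two-tailed significance level (α) of 0.05". An unequal-variance t-test gives power 0.7999 at 140 per arm and 0.8027 at 141, so 141 is reproduced. The total is 2 × 141 / 0.8 = 352.5, rounded up to 353. The sample size arithmetic is sound; the issue is possible bias. About 176 per arm are randomised (353 / 2 = 176.5).

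**What remains obtainable after the rule is applied.**

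| Outcome | Stated source | Needs her reply? |
|---|---|---|
| Exclusive breastfeeding | Questionnaire, checked against formula records | Not for the record check |
| Prolactin, IGF-I | Ward blood draw | No |
| On-demand feeding | No record source stated | Probably |
| Postpartum emotion, intention | Questionnaires via WeChat | Yes |

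**How often the rule could fire.** The protocol gives "We will include primiparous pregnant women at 34–38 gestational weeks" and a task every 2 days. Assuming delivery at 40 weeks, the number of occasions is (40 − entry week) × 7 / 2: 21, 14 or 7 for entry at 34, 36 or 38 weeks. If misses are independent and three cumulative misses trigger the rule, the chance is P(Binomial(n, p) ≥ 3):

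| Assumed miss rate | n = 21 | n = 14 | n = 7 |
|---|---|---|---|
| 10% | 35% | 16% | 3% |
| 20% | 82% | 55% | 15% |

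The definition matters as much as the miss rate. Over 17 occasions (5 weeks) at a 10% miss rate, the chance is 24% if three is cumulative and about 1% if the three must be consecutive.

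**Illustrative bias with no true effect.** All inputs are assumed except the number per arm, which follows from the target of 353: 50% exclusive breastfeeding in both arms, 30% among those removed, 176 per arm. With a fraction m removed, the rate among those kept is (0.50 − 0.30m)/(1 − m). For example, m = 0.25 gives (0.50 − 0.075)/0.75 = 56.7%, and m = 0.15 gives (0.50 − 0.045)/0.85 = 53.5%. The standard error is √[p₁(1 − p₁)/n₁ + p₂(1 − p₂)/n₂] with n = 176(1 − m). With z = difference / standard error, the two-sided error is 1 − Φ(1.96 − z) + Φ(−1.96 − z).

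| Removed, by arm | Rates among those kept | Spurious difference | Two-sided type I error |
|---|---|---|---|
| 20% vs 20% | 55.0% vs 55.0% | 0 points | 5.0% |
| 22% vs 18% | 55.6% vs 54.4% | 1.3 points | 5.5% |
| 25% vs 15% | 56.7% vs 53.5% | 3.1 points | 8.3% |
| 30% vs 10% | 58.6% vs 52.2% | 6.3 points | 18.7% |

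**Sensitivity to the assumed prognosis.** With 40% instead of 30% exclusive breastfeeding among those removed, 25% versus 15% gives 1.6 points and 5.8%. In another model, 30% of each arm are less motivated and all removals come from that group. Exclusive breastfeeding is 55% versus 30%, or 60% versus 20%, in more and less motivated women. Removing 25% versus 15% then gives 2.7 to 4.4 points and 7.5% to 11.5%; removing 30% versus 10% gives 5.6 to 8.9 points and 15% to 32%.

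**Information.** If all 176 per arm contributed a LATCH score, power at a difference of 0.66 would be about 88% instead of 80%. This is an upper bound: it assumes no other attrition and no dilution from including non-adherers.

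**The case against.** Four points can fairly be made on the other side.

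1. **Exclusion from analysis is not stated.** A reader might infer that the protocol drops these women and compares compliers only. No sentence says so, no analysis set is named, and an analysis plan not at hand could keep them. The 20% allowance shows that attrition was expected, not that record-based outcomes would be discarded. This stands. But the ordinary meaning of the term is that outcomes cease to be collected, and no section says that these women are still followed.
2. **The trigger may be unreachability.** A reader might take the rule to mean three skipped writing tasks. It follows the hints and encouraging messages and is justified by not disturbing women, so it could equally mean three unanswered contacts. That would be nearer to genuine loss to follow-up. This stands as an ambiguity. Even then, formula records and ward samples do not need her reply.
3. **Not every feeding outcome is recoverable.** On-demand feeding has no stated record source, and the 1-week questionnaire uses the channel on which she has stopped answering. This stands, and it limits the claim to exclusive breastfeeding and the hormones.
4. **Bias is not certain.** The same rule, prompts and themes apply to both arms. If equal proportions with equal prognosis are removed, the bias is zero. This also stands: the protocol gives no arm-specific removal rates, so the differential scenarios are illustrations.

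**Conclusion.** The concern holds in a limited form. The protocol fixes a rule that merges stopping the task with loss to follow-up and leaves its trigger undefined. Its stated reason covers only stopping the messages. Followed as written, and in the ordinary meaning of the term, it would remove non-adherers from the randomised comparison, although exclusive breastfeeding and the hormones can be obtained without the writing task. Recovery of on-demand feeding and the questionnaire outcomes is uncertain.

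Under the main assumptions the spurious difference runs from zero (equal removal and equal prognosis) through 3.1 points with a type I error of about 8% (25% versus 15% removed) to 6.3 points and about 19% (30% versus 10%). The breastfeeding and removal rates behind these figures are assumed; none is trial data. The documents do not support saying that these women are definitely excluded from analysis, that all feeding outcomes remain available, or that the result will be biased.

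**What to change.** Replace the sentence in Intervention so that it does the following:

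- It defines three non-responses: missed questionnaires or unanswered prompts, cumulative or consecutive.
- After that point, writing prompts and reminders stop, and the woman is recorded as having discontinued the intervention.
- Formula records, ward blood samples and the single 1-week questionnaire are still collected unless she withdraws consent.
- Every randomised woman with outcome data is analysed in her allocated arm.
- *Lost to follow-up* is reserved for women with no postnatal outcome.

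The cost is a rewritten rule and one questionnaire sent to women who stopped writing, which keeps to the aim of not disturbing them unduly. On-demand feeding and the questionnaire outcomes will still have some missing data. The estimate will include non-adherers and may look smaller.

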### Evaluation and outcomes

Primary outcomes will include exclusive breastfeeding and on-demand feeding during postnatal hospitalisation. Exclusive breastfeeding means that the baby is not given any liquid or solid food other than breast milk. This indicator will be included in the postnatal questionnaire and also be double-checked in the hospital care records of formula. On-demand feeding means breastfeeding according to the baby’s needs. Since the infant’s early urination reflects breastfeeding, changing diapers 6–8 times a day in the early postpartum period is considered feeding on demand.

Secondary outcome indicators will mainly include other breastfeeding behaviours during postpartum hospitalisation (first postnatal food for babies is breast milk; LATCH breastfeeding score), lactation-related hormone secretion (prolactin and IGF-I) and postpartum breastfeeding intention and postpartum emotion.

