## Abstract

**Introduction:**

Though evidence has revealed the beneficial effects of cognitive improvement interventions on breastfeeding, the effect of psychological interventions has rarely been studied. This study aims to test whether promoting a positive emotion intervention, ‘Three Good Things’ intervention, during the last trimester of pregnancy can enhance early colostrum secretion and breastfeeding behaviours by modulating the hormones associated with lactation (prolactin and insulin-like growth factor I). We will attempt to promote exclusive breastfeeding by using physiological behavioural measures.

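### Two primary outcomes are named with no success rule; if either one suffices at two-sided 0.05, the family-wise type I error lies between 5% and 10%

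*Protocol article*

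**What the plan says.** In the protocol article, Evaluation and outcomes opens with: "Primary outcomes will include exclusive breastfeeding and on-demand feeding during postnatal hospitalisation". Each outcome is then defined. Exclusive breastfeeding comes from the postnatal questionnaire and is cross-checked against the hospital's formula records. On-demand feeding is inferred from a daily diaper count of 6 to 8, and no records check is described for it. The two are given no order, no share of alpha and no rule for combining them. LATCH is listed among the secondary outcomes.

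Data analysis chooses tests by type of data: a t-test or rank-sum test for quantitative data and a χ² test for qualitative data. It gives no significance level and no rule covering more than one primary test.

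The one significance level in the article is under Sample size, "a two-tailed significance level (α) of 0.05", and there it serves a calculation on LATCH: "Given the breastfeeding behaviour score (LATCH) was 12.72 in the intervention group (SD=2.33) and 12.06 in the control group (SD=1.51").

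The Abstract states the purpose partly as "We will attempt to promote exclusive breastfeeding by using physiological behavioural measures". The Aims and Hypothesis 1b speak more broadly of breastfeeding behaviours.

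**The concern.** With two primary outcomes, the rule linking them determines what a positive trial means. If one significant result is enough, two chances at 0.05 push the false-positive rate for the main claim above 5%. If both are needed, that rate is held, but the trial is harder to win and power has to be considered jointly. The article does not say which applies.

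The choice matters here because the two outcomes are not equally well measured: one has a check against care records and the other rests on a diaper count. Under an either-one reading, the trial could be called positive on the count alone while exclusive breastfeeding showed no effect. Hypothesis 1b is worded broadly enough to allow that reading, and nothing in the article rules it out.

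**Working it through.** **Inputs.** Two primary outcomes (Evaluation and outcomes). Alpha 0.05 two-sided, power 80%, LATCH means 12.72 and 12.06 with SDs 2.33 and 1.51, 141 per arm, 20% dropout, 353 in total (Sample size). The correlation between the two primary test statistics is not given, so a range is assumed.

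**1. The plan's own figure.** Normal approximation:

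n per arm = (2.33² + 1.51²) × (1.960 + 0.842)² / (12.72 − 12.06)² = 7.709 × 7.849 / 0.4356 = 138.9, so 139.

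With the unequal-variance t-test that the article names, power is 0.7999 at 140 per arm and 0.8027 at 141, which gives 141. Dropout: 282 / 0.80 = 352.5, so 353. Both stated figures reproduce. They confirm that 0.05 was used for a single test of LATCH, with no allowance for two primary tests.

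**2. Either outcome suffices, each at 0.05.** With neither outcome affected by the intervention:

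- Independent tests: 1 − 0.95² = 0.0975.
- Upper bound for any dependence: 0.05 + 0.05 = 0.10.
- Correlated tests: 1 − P(|Z₁| ≤ 1.96 and |Z₂| ≤ 1.96), bivariate normal with correlation ρ.

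| Assumed ρ | Family-wise error |
|---|---|
| 0 | 9.75% |
| 0.3 | 9.5% |
| 0.5 | 9.1% |
| 0.7 | 8.3% |
| 0.8 | 7.8% |
| 0.9 | 7.0% |
| towards 1 | towards 5% |

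**3. Both must be significant.** A false claim needs a wrongly significant result on at least one outcome without a true effect, so its probability is at most 5%. Joint power cannot exceed the lower of the two single powers. As an illustration, two independent tests with 80% power each give 0.80 × 0.80 = 64%.

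**4. After a rule is fixed.**

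- Fixed sequence: the second test is reached only if the first is significant. If the first outcome has no true effect, the error is at most 5%. If it has one, only the second test can err, again at most 5%.
- Holm: the smaller p-value must meet 0.025 and then the larger 0.05. With no effect on either, the error is at most 2 × 0.025 = 5%, or 1 − 0.975² = 4.94% if independent.

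**5. Cost of the stricter first step under Holm.** With 141 per arm and 80% power, the detectable increase in a proportion is:

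| Assumed control rate | At 0.05 | At 0.025 |
|---|---|---|
| 30% | 16.2 points | 17.9 points |
| 50% | 16.4 points | 18.0 points |
| 70% | 14.0 points | 15.3 points |

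The control rates are assumptions; the article gives none for either primary outcome.

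**The case against.** The strongest reply is that this is a condensed journal article. A full protocol or analysis plan may exist, and an adjustment method such as Holm often sits there. That stands as far as the method goes: its absence alone would be weak evidence. It does not cover the success rule. Whether one outcome or both decide the trial is part of defining the primary outcomes, and the article defines them without it.

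A reader might infer that the plan tests each primary at 0.05, lets either one win, and so carries a false-positive risk close to 10%. The documents do not support that as a statement of fact:

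- No level is attached to either primary; 0.05 belongs to the LATCH calculation.
- No either-one rule is written. The outcomes are joined by a plain conjunction, and a both-must-succeed rule would cause no inflation.
- The figure near 10% is the independence case. Both outcomes are feeding behaviours in the same mother-infant pairs over the same stay, so positive correlation is plausible and would lower it.
- The χ² test is assigned to a type of data, not to these outcomes by name, although both are categorical as defined.

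A reader might also take the verb in "Primary outcomes will include exclusive breastfeeding and on-demand feeding during postnatal hospitalisation" as leaving the primary family open. That is a matter of wording only: two items are named and each is then defined, so the natural reading is a list of two.

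**Conclusion.** The point holds in conditional form. The article names two unranked primary outcomes and provides only unadjusted tests by data type, so followed as written it yields two primary tests and no rule for reading them together. If each is tested at two-sided 0.05 and either suffices, the family-wise error lies between 5% and 10%: 9.75% under independence, about 9.1% at correlation 0.5 and 7.8% at 0.8. If both must succeed, the error is at most 5% and the consequence is lower joint power instead. The first result assumes the per-test level, the either-one rule and the correlation, none of which the article states. That the success rule is undefined requires no assumption.

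**What to change.** State the success rule alongside the primary outcomes. Any one of these would do:

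1. **Fixed sequence.** Test exclusive breastfeeding first at two-sided 0.05, since it is the outcome verified against care records, and test on-demand feeding at 0.05 only if the first is significant. This costs no alpha on the first test, but on-demand feeding alone can no longer carry the trial.
2. **Holm across both at an overall 0.05.** Either outcome can still win, but the smaller p-value must meet 0.025. At 141 per arm this raises the detectable increase by about 1.3 to 1.7 points over the assumed control rates above.
3. **Both must be significant, each at 0.05.** No adjustment is needed, but joint power is lower than for either outcome alone.

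Making exclusive breastfeeding the sole primary outcome is a further possibility, but the point does not depend on it.

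The change is to wording and the registry entry; no new data are needed. Study design places the formal trial in January 2022, so recruitment may already have begun. In that case, make the change before any between-group outcome data are examined, and record it with its date in the registry.

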### Data collection and follow-up

On the day of enrolment, pregnant women will be asked to complete an enrolment questionnaire providing information about general demographic characteristics and other factors influencing breastfeeding. Meanwhile, if the enrolment questionnaire finds prenatal depression among the participants, we will refer them to the department of psychology. Then, the ecological instantaneous evaluation of both groups will be performed every week to determine the trend of change in intention and emotions until delivery. The measurement of emotion uses the Positive and Negative Affect Scale (PANAS) and 10 positive items for positive emotions proposed by Fredrickson for validation.^24 25^ Postpartum questionnaires on breastfeeding behaviour during postnatal hospitalisation will be completed 1 week after delivery. Blood samples will be collected twice, after they are admitted to the hospital approaching delivery and after delivery at 7 to 8 am (vaginal delivery: the morning after one night; caesarean section: the morning after two nights), and evaluated for prolactin and IGF-I to evaluate postpartum lactation ability. The blood draw will be conducted by nurses in the ward.

On recruitment, general demographic variables will be collected: education, occupation, number of permanent household members, total average annual household income and expected date of birth. Other influencing factors will include mode of delivery, self-reported ease of breastfeeding, degree of sleep disturbance, self-reported importance of early exclusive breastfeeding, knowledge of breastfeeding, birth injury and nipple cracking pain scores, degree of hospital support, depression (measured by Edinburgh Postnatal Depression Scale, EPDS), anxiety (measured by Generalised Anxiety Disorder, GAD-7), breastfeeding intentions (measured by Infant Feeding Intentions Scale, IFI), breastfeeding behaviour score (LATCH), resilience (Brief Resilience Scale, BRS) and potential number of traumatic events.^26–31^ Generally, Baby-Friendly hospitals will take measures such as early sucking and skin-to-skin contact within 1 hour after delivery, limitation of bottle used, room-in, etc.^32^ We will also record and report routine measures taken in this Baby-Friendly hospital.

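### The primary outcome on-demand feeding is defined as cue-led breastfeeding but scored by a diaper count that captures neither cue-led feeding nor breastfeeding

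*Protocol article*

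**What the plan says.** All of the relevant wording on the outcome is in the protocol article, under Evaluation and outcomes.

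- Status: "Primary outcomes will include exclusive breastfeeding and on-demand feeding during postnatal hospitalisation".
- Definition: "On-demand feeding means breastfeeding according to the baby’s needs".
- Scoring rule: "changing diapers 6–8 times a day in the early postpartum period is considered feeding on demand". The reason given is "Since the infant’s early urination reflects breastfeeding".
- Formula use is recorded, but the check belongs to the other primary outcome. Of exclusive breastfeeding the article says: "This indicator will be included in the postnatal questionnaire and also be double-checked in the hospital care records of formula". No such check is attached to on-demand feeding.

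Under Data collection and follow-up, the timing is: "Postpartum questionnaires on breastfeeding behaviour during postnatal hospitalisation will be completed 1 week after delivery". The article does not say how counts above 8 are scored, which day or days the count refers to, or whether the diaper rule has been compared with observed or reported feeding on cue.

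**The concern.** The definition has two parts: the baby is breastfed, and feeds follow the baby's needs. The scoring rule observes neither. It counts diaper changes, which depend on how much fluid the baby takes, whatever its source and whatever prompted the feed. Under the rule as written, a mother who feeds by the clock and changes seven diapers is scored as feeding on demand. So is a baby topped up with formula who has the same count, even though that baby fails the other primary outcome.

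The trial's hypotheses concern breastfeeding behaviour. If this outcome shows a difference, the difference may lie in fluid intake or diaper habits. If it shows none, a real change in feeding on cue may have been lost in misclassification. Recruiting more women would restore some precision but would not change what is measured.

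**Working it through.** **1. Definition against rule.**

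| Element of the definition | What the rule observes |
|---|---|
| Breastfed | Nothing. No condition on what was fed is stated, and formula records are tied to exclusive breastfeeding only |
| According to the baby's needs | Nothing. No item on cues or schedule is stated |
| (not in the definition) | A daily diaper count between 6 and 8 |

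The link between the columns is the statement that early urination reflects breastfeeding. At most this supports the count as a sign of intake. It does not separate cue-led from scheduled feeding, or breast milk from formula.

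**2. The plan's own sample size.** This sets the number per arm used in step 3. The Sample size section uses the LATCH score, a secondary outcome: means 12.72 (SD 2.33) and 12.06 (SD 1.51), with "statistical power (1−β) of 80%, and a two-tailed significance level (α) of 0.05".

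- Difference: 12.72 − 12.06 = 0.66. Sum of variances: 2.33² + 1.51² = 7.709.
- Normal approximation: n = 7.709 × (1.960 + 0.842)² / 0.66² = 138.9, so 139 per arm.
- Exact noncentral t with Satterthwaite degrees of freedom: 140 per arm gives 79.99% and 141 gives 80.27%, so 141 per arm.
- Dropout: 282 / 0.8 = 352.5, so 353 in total.

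The stated 141 and 353 reproduce. They say nothing about power for on-demand feeding.

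**3. Illustration of dilution (assumed inputs).** Assume true on-demand rates of 50% and 65%, 141 analysed per arm, and the same sensitivity (Se) and specificity (Sp) in both arms. None of these rates or accuracies comes from the documents.

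The observed rate is Se × p + (1 − Sp) × (1 − p), so the observed difference is the true difference × (Se + Sp − 1). Power is for the two-sided 5% comparison of two proportions, with pooled variance under the null and unpooled variance under the alternative: Φ{[d − 1.96 √(2p̄(1−p̄)/n)] / √[(p₁(1−p₁) + p₂(1−p₂))/n]}.

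| Se = Sp | Observed rates | Difference | Power |
|---|---|---|---|
| 1.0 | 50.0% vs 65.0% | 15 points | 72% |
| 0.9 | 50.0% vs 62.0% | 12 points | 53% |
| 0.8 | 50.0% vs 59.0% | 9 points | 33% |

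For the first row: p̄ = 0.575; (0.15 − 1.96 × 0.0589) / 0.0582 = 0.59; Φ(0.59) ≈ 0.72.

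**4. The upper limit, read literally (assumed Poisson counts).** At a mean of 7 changes a day, 43% of babies fall in 6–8 and 27% exceed 8. At a mean of 9, 34% fall in the range and 54% exceed it. If counts above 8 were scored as no, the share scored as on demand would fall as output rose past the range.

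**The case against.** The strongest reply is that a journal article condenses a longer protocol and a questionnaire that are not shown. The diaper sentence may be meant to apply only to breastfed babies, since the sentence before it restricts the term to breastfeeding. Feeding type is known for each baby, so a coding rule could already remove formula-fed babies. The questionnaire may already ask about feeding on cue. The choice of assessment day is also a detail that an article may leave out.

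Part of this stands. The article does not say that a formula-fed baby is scored yes; it states no condition that prevents it. The missing day alone would be a small matter. But the main point is not an omission. The article does state a scoring rule, and that rule conflicts with the definition just before it. Restricting the rule to breastfed babies would still leave scheduled feeding counted as on demand.

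Three stronger readings are tempting, and the documents do not support them.

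- A reader might infer that the plan scores nine changes as a failure. It does not say so. The range may have been meant as typical, or as at least 6. The upper limit is unclear, and only the literal reading excludes higher counts.
- A reader might infer from Data collection and follow-up that hospital stay differs by mode of delivery. That section gives the timing of the blood draw (after one or two nights) and no length of stay.
- A reader might infer that formula top-ups in the control group could reverse the effect. That needs unequal error between arms, and no figure in the documents shows more top-ups in controls. The dilution formula used here assumes equal error.

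**Conclusion.** The point holds as a conflict between a primary outcome's definition and its scoring rule. As written, the rule can score scheduled feeding, and feeding with formula, as on-demand breastfeeding, so a result on it could not be interpreted as the outcome it is named for. This follows from the text and needs no assumed number.

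The size is not known. The loss of power from about 72% to 53% or 33% illustrates error of a given amount that is equal in both arms. It is not an estimate for this trial, and 72% is not a planned power, because the 141 per arm was set for LATCH. Exclusive breastfeeding, the other primary outcome, is clearly defined, checked against records and unaffected.

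**What to change.** - Score on-demand feeding from a direct item in the 1-week postpartum questionnaire: breastfed when the baby showed hunger cues, breastfed by schedule, or mainly formula.
- Use the formula data already collected so that formula-only babies count as no, and state in advance how mixed feeding is classified.
- Keep the diaper count as a supportive secondary measure, for a stated postnatal day and with a lower threshold only.
- For women already assessed without the item, report the diaper measure restricted by the formula records, and label it an indicator of intake.

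The cost is one questionnaire item and revised outcome wording. There are two downsides. The item is self-reported with a week's recall, so it has error of its own. The Study design section dates the formal trial to January 2022, so the definition would change after the start; the change must be dated and made without looking at outcomes by arm.
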